## **SCREENING PROCEDURE**

A member of the site research team will screen candidates for enrolment. Subjects will be recruited from those patients listed for their first catheter ablation of AFL.

## **INFORMED CONSENT AND ENROLMENT**

If the physician agrees, a member of the investigational site research team will discuss with the subject and any family members/significant others the study's purpose, procedures and follow-up requirements and provide written information approved by the Ethics committee prior to enrolment. All subject questions will be answered and if the subject agrees, written informed consent as approved by the Ethics Committee will be obtained. Failure to provide informed consent excludes the subject from the study. Enrolment occurs when informed consent has been signed and the patient has been randomly allocated to a treatment strategy.

## **INCLUSION CRITERIA**

- Age  $\geq 18$  years
- Documented paroxysmal or persistent AFL

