## **STUDY PROTOCOL**

### Pre –procedure

Study participants will be randomized using block envelopes to undergo the procedure either blinded (control) or un-blinded to contact force or ECI. CARTO-3 or NAVx Velocity will be used as the 3D mapping systems for contact force and ECI catheters respectively. The procedures will be performed with patients in the post-absorptive state under conscious sedation or general anaesthesia.

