#### Outcome measures

Primary outcome: Time to achieve bi-directional block(secs) . This is defined as the time from the first lesion to the time that consistent (> one minute) bidirectional block is achieved.

Total RF energy required for the whole procedure (sec), and total energy required for ablation (power x ablation time in secs).

Secondary outcomes: complications during initial hospitalisation and during six month follow up, isthmus re-conduction during the 30 minute waiting period, total procedure time, procedural cost, fluoroscopy time,

radiation exposure, total radiofrequency energy delivered, and long term success rate (freedom from AFL episodes of >30seconds duration following discontinuation of anti-arrhythmic medication), isthmus re-conduction at repeat procedure.

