### Statistical methods

Continuous variables will be checked for normality. If they are normally distributed the results will be expressed as mean  $\pm$  SD and compared by Student's t-test or ANOVA. If they are skewed the results will be expressed as median and interquartile range, and compared using the Mann Whitney U test. A chi-squared test will be used to compare categorical variables. A p value <0.05 will be considered statistically significant. Alternative statistical methods and additional analyses will be conducted as deemed appropriate.

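### The stated comparison of time to bidirectional block takes no account of rhythm at the first lesion, which costs precision and leaves small groups open to chance imbalance

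*Protocol*

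**What the plan says.** Under Inclusion criteria, the protocol requires "Documented paroxysmal or persistent AFL" and sets no condition on the rhythm in which the patient reaches the laboratory.

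Under Outcome measures, the primary outcome is time to bidirectional block in seconds: "This is defined as the time from the first lesion to the time that consistent (> one minute) bidirectional block is achieved". Rhythm at the first lesion is not mentioned. The section on patient preparation and procedure describes catheters, energy settings and the waiting period, but does not say that the starting rhythm is standardised or noted.

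Under Pre-procedure, allocation is described as follows: "Study participants will be randomized using block envelopes to undergo the procedure either blinded (control) or un-blinded to contact force or ECI". No stratification factor appears in the text. Figure 2, on the randomisation process, is not shown.

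Under Statistical methods, normally distributed outcomes are compared by t-test or ANOVA, and skewed ones are "compared using the Mann Whitney U test". No covariate is named. The threshold is a p value below 0.05, and the section closes with an open clause: "Alternative statistical methods and additional analyses will be conducted as deemed appropriate".

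**The concern.** The two eligible flutter types suggest two starting situations. Some patients will be in sinus rhythm at the first lesion, so isthmus conduction can be tested by pacing as ablation proceeds. Others will be in flutter, where pacing cannot demonstrate block until the flutter has ended. Since the clock starts at the first lesion in both, the interval may include a delay that depends on rhythm and not on contact sensing. The protocol does not state this mechanism. It is general electrophysiological reasoning and makes the effect plausible, not established.

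If the effect exists, it adds variance to the primary outcome that the stated tests leave in the error term. In groups of about 30, one group may also contain noticeably more patients ablated in flutter than another. A reader of that single trial could not separate the imbalance from the effect of the catheter information.

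Timing matters too. A covariate can be chosen in a later analysis plan, but only if the rhythm was written down during the procedure.

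**Working it through.** **The plan's own figures.** Sample Size gives 30 per group and 120 in total: 120 / 30 = 4 groups. Funding agrees: 120 x (£300 + £100) = £48,000. No SD, effect size or power is stated, so there is no power calculation to reproduce, and effects below are in SD units.

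**Inputs.**
- From the protocol: n = 30 per group (60 v 60 if two groups are pooled on each side) and alpha 0.05, taken as two-sided because sidedness is not stated.
- Assumed: share p ablated in flutter, 30-70%; rhythm effect d of 0, 0.5 or 1.0 within-rhythm SD.

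**1. Chance imbalance.** With X1 and X2 independent Binomial(n, p), the exact probability that the shares differ by 20 points or more is:

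| Comparison | p = 0.3 or 0.7 | p = 0.5 |
|---|---|---|
| 30 v 30 (gap of at least 6 patients) | 0.120 | 0.155 |
| 60 v 60 (gap of at least 12 patients) | 0.022 | 0.035 |

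**2. What an imbalance does in one trial.** The estimated difference moves by imbalance x d. At 20 points this is 0.20 x 0.5 = 0.10 SD, or 0.20 x 1.0 = 0.20 SD. The standard error of a 30 v 30 difference is sqrt(2/30) = 0.26 SD, so the movement is below one standard error.

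**3. Bias and type I error.** In 40,000 simulated trials per setting (p = 0.5), the mean difference under no treatment effect was within 0.002 SD of zero, and unadjusted type I error was 0.049-0.050 for every d. Only among the 30 v 30 trials that happened to be imbalanced by 20 points or more was it higher: 0.064 at d = 0.5 (0.070 in a repeat with 400,000 trials) and 0.11 at d = 1.0.

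**4. Precision.** Rhythm's share of the outcome variance is p(1-p)d² / (1 + p(1-p)d²). At p = 0.5:
- d = 0.5: 0.0625 / 1.0625 = 0.059
- d = 1.0: 0.25 / 1.25 = 0.200

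At p = 0.3 the values are 0.050 and 0.174.

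**5. Power at 30 v 30.** The reference effect is the difference detectable with 80% power by the normal approximation: (1.960 + 0.842) x sqrt(2/30) = 0.72 SD. It is a yardstick, not a protocol figure. Unadjusted, the outcome SD is sqrt(1 + 0.25d²) at p = 0.5, and the noncentrality is 0.723 x sqrt(15) / SD.

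| Rhythm effect d | Outcome SD | Noncentrality | Power unadjusted | Power adjusted |
|---|---|---|---|---|
| 0 | 1.000 | 2.80 | 0.79 | 0.78 |
| 0.5 | 1.031 | 2.72 | 0.76 | 0.78 |
| 1.0 | 1.118 | 2.51 | 0.69 | 0.78 |

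The unadjusted column uses the noncentral t distribution with 58 degrees of freedom. Simulation gave 0.785, 0.763 and 0.696 unadjusted, and 0.776-0.778 adjusted. At 60 v 60, with the corresponding reference effect of 0.51 SD, simulated power was 0.768 and 0.705 unadjusted (d = 0.5 and 1.0) against 0.79 adjusted. Pooling therefore makes large imbalance rare but does not remove the loss of precision.

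**The case against.** The strongest reply is that nothing here is an error. An unadjusted comparison of randomised groups is valid, one outcome definition applies to every group, and the study is described as a feasibility study. Choice of covariates commonly belongs in a statistical analysis plan, which may exist, and the open clause under Statistical methods leaves room for one. All of this is correct, and it limits the point to efficiency. It does not dispose of it: a later plan cannot adjust for a rhythm that was not recorded, and adjustment chosen under an open clause once the data are seen is weaker than adjustment fixed beforehand.

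A reader might infer three stronger things that the documents do not support.

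- That the primary result is biased. Chance imbalance under randomisation is already covered by the test's error rate, as step 3 of the working shows.
- That rhythm is used nowhere in the trial. This can be said only of the visible text, because Figure 2 and the case record form are not shown.
- That rhythm is a known strong predictor, or that the inclusion criterion settles each patient's rhythm. The protocol quantifies neither the rhythm effect nor the share ablated in flutter. Paroxysmal or persistent type is only a proxy for rhythm at ablation.

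It is also fair that the loss is small at the lower end: about 2 points of power at 0.5 SD, and none if rhythm has no effect.

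**Conclusion.** The point holds as one of precision and of protection against an unlucky allocation. The visible text fixes an unadjusted comparison of an outcome to which rhythm at the first lesion plausibly contributes. The loss at 30 v 30 is roughly 2 points of power if the rhythm effect is 0.5 SD and 9 points if it is 1.0 SD (0.78 adjusted against 0.76 and 0.69). Both effect sizes and the 50% flutter share behind these power figures are assumptions. The power figures are for t-test and linear-model analyses on a scale where the outcome is roughly normal; a rank test would give somewhat different values. The point is worth acting on because the remedy is nearly free and has to be in place before procedures are done.

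**What to change.** Record rhythm at the first lesion, as flutter or sinus/paced, on the laboratory case record form if it is not already there. In the protocol or the analysis plan, before outcome data are examined, name it as a covariate or stratum in the comparison of time to bidirectional block, for example ANCOVA on log time or a rank test stratified by rhythm. Use rhythm itself, not paroxysmal or persistent type.

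The cost is one form item and one degree of freedom. If rhythm turns out not to matter, the loss of power at 30 v 30 is under 1 point (0.785 unadjusted against 0.777 adjusted in simulation). No extra patients or procedures are required, and the envelopes need not be stratified.

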## **EXCLUSION CRITERIA**

- Inability or unwillingness to receive oral anticoagulation
- Previous ablation procedure for AFL
- Unwillingness or inability to complete the required follow up arrangements
- Concomitant atrial fibrillation

## **STUDY PROTOCOL**

### Pre –procedure

Study participants will be randomized using block envelopes to undergo the procedure either blinded (control) or un-blinded to contact force or ECI. CARTO-3 or NAVx Velocity will be used as the 3D mapping systems for contact force and ECI catheters respectively. The procedures will be performed with patients in the post-absorptive state under conscious sedation or general anaesthesia.

### Patient preparation and procedure.

As per standard practice, oral anticoagulation will be administered to the majority of patients who will then go on to have the procedure performed with uninterrupted warfarin (INR 2-3.5). Depending on randomisation, either the Ensite or CARTO-3 mapping system will be used, and the respective reference patches will be applied to the patient in the cardiac catheter laboratory. Venous sheaths will be inserted into the right and/or left femoral veins. A decapolar catheter will be inserted into the coronary sinus, and a quadripolar catheter into the right ventricle. An additional 20 pole Halo diagnostic catheter (Biosense Webster, Diamond Bar CA, US) can be placed around the tricuspid valve annulus as per operator preference. The creation of three dimensional right atrial geometry will be left to the discretion of the operator and is not a requirement.

A flutter line will be created by either a drag approach or point by point ablation using an irrigated tip Thermocool Smart Touch (Biosense Webster, Diamond Bar CA, US), or an Ensite Verisense catheter (St Jude Medical, St Paul MN, US). In the control group the operator will be blinded to contact force or ECI, by closing the respective sensing information windows on the 3D mapping system. Energy will be delivered at each point for a minimum of 30 seconds with flow limited to 17ml/min and power limited to 40W with a maximum temperature of 48°C. If bidirectional block is not achieved on the first pass, additional ablation targeting gaps will be applied. Following bidirectional block, a waiting time of 30minutes will be observed to check for, and react to, isthmus re-conduction. The procedure will end at this stage.

#### Data Collection

All data will be recorded on a paper case record form in the catheter laboratory, and later transferred onto an electronic database.

#### Post Procedure Management

Patients will be kept on telemetry for 4 hours post procedure, and mobilised following this. Patients will be discharged as per local established practice and depending on the patients well being. All anti-arrhythmic medications will be discontinued, but warfarin will be maintained for a minimum of two months.

#### Contact Force pressures and ECI

Because contact force sensing and ECI catheters are a new technology, there are limited data on which to base recommendations as to appropriate forces to use whilst ablating. There are some data to suggest that very high pressures are more likely to cause cardiac perforation and that the pressure required to perforate the heart is lower whilst ablating than when mapping. For the Smart Touch catheter Contact force pressures of less than 40g appear to be safe with a margin of error that is likely to be large (i.e. pressures considerably higher than this are probably also safe in the majority of cases). Conversely, low pressures are more likely to be associated with ineffective lesion formation. In order to try to ensure safe and effective use of the Smart Touch catheter, a contact force range of 5–40g will be recommended. For the Verisense catheter a change in ECI of 12% will be aimed for, as this appears to be the optimal value for safe full thickness lesion formation. Values above 12% have been associated with collateral tissue injury. A visual warning on the CARTO navigation system will be programmed to occur if pressures exceed 50g. Early studies have shown wide intra-operator variability in terms of level of force used, and pressures can be affected by factors such as cardiac contraction and where the catheter is positioned anatomically. Therefore the final decision about whether to ablate at any given contact force measurement and power setting will be left to the discretion of the operator. As further evidence emerges as to the ideal pressures and ECI index to use, it is likely that a range of pressures will be recommended but this range will not be prescriptive for the study.

#### Follow up

Patients will be followed up at three and six months post procedure. A seven day ambulatory ECG will be recorded prior to the follow up visit. All patients who experience a recurrence will be offered a repeat electrophysiological study if clinically indicated.

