## **STUDY DESIGN**

In order to examine these hypotheses we aim to perform a multicentre prospective, randomised study comparing RF energy time, procedure duration and outcome of catheter ablation of AFL between non-contact 3D guided ablation (i.e. blinded to contact or ECI sensing), contact force sensing and the assessment of ECI. Patients will be followed up for 6 months post procedure.

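### No masking is specified for reading the ambulatory ECGs that decide long-term freedom from atrial flutter

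*Protocol*

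**What the plan says.** - **Outcome.** Protocol, Outcome measures, lists among the secondary outcomes the "long term success rate (freedom from AFL episodes of >30seconds duration following discontinuation of anti-arrhythmic medication".
- **Ascertainment.** Protocol, Follow up: "Patients will be followed up at three and six months post procedure", and "A seven day ambulatory ECG will be recorded prior to the follow up visit". No reader or reading procedure is named, and nothing is said about what the reader knows of the allocation.
- **Blinding.** The word is used only for the operator's view of the sensing data. Study design describes the control as "non-contact 3D guided ablation (i.e. blinded to contact or ECI sensing", and Patient preparation and procedure says "In the control group the operator will be blinded to contact force or ECI", done by closing the sensing windows on the mapping system. This is how the control procedure is delivered. It does not hide the arm from anyone who later judges an outcome.
- **Expectation.** Hypothesis 1 predicts improved outcomes with either sensing technology compared with the conventional approach.

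**The concern.** Long-term success depends on a reading. Someone must decide whether an episode on the recording is AFL and whether it lasts more than 30 seconds. Only AFL counts, so an episode read as atrial fibrillation, or as just too short, leaves the patient a success.

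A reader who knows the arm, and knows that sensing is expected to do better, may settle unclear episodes in that direction without meaning to. If error in reading depends on the arm, no later analysis can separate it from a treatment effect. The operator has to see or not see the sensing display, so cannot be masked to it. The person reading a recording made three or six months later can be masked. Whether that person is masked is a matter of trial conduct to settle before the first recording is read, so a separate analysis plan would not ordinarily deal with it.

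**Working it through.** **Inputs from the protocol**
- Sample size: 120 in total, 30 per group (Sample Size). Check: 120 / 30 = 4 groups. The budget agrees: 120 x (£300 + £100) = £48,000 (Funding).
- Long-term recurrence: 5-10%, at a mean follow-up of eight months (Catheter ablation of atrial flutter). Follow-up here is six months.
- Test: chi-squared for categorical variables, p < 0.05 (Statistical methods).

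The protocol gives no power calculation for long-term success, so there is no stated figure to reproduce beyond the group sizes.

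**Step 1. Expected events per arm.** 30 x 0.05 = 1.5 and 30 x 0.10 = 3.

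**Step 2. Weight of one call.** Suppose a patient's status rests on a single episode. Reclassifying it moves the arm's success rate by 1/30 = 3.3 percentage points. As a share of the expected events, that is 1/3 = 33% to 1/1.5 = 67%.

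**Step 3. Can a few calls create a significant result?** Start from equal counts and change k calls, all in favour of sensing: a control patient moved to recurrence, or a sensing patient moved to success. The table gives the smallest uncorrected chi-squared p over all ways of splitting the k calls, at 30 v 30.

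| Equal start | k = 1 | k = 2 | k = 3 | k = 4 |
|---|---|---|---|---|
| 1 v 1 | 0.313 | 0.150 | 0.076 | 0.038 (4 v 0) |
| 2 v 2 | 0.554 | 0.150 | 0.076 | 0.038 (4 v 0) |
| 3 v 3 | 0.640 | 0.301 | 0.076 | 0.038 (4 v 0) |

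At least four calls, all in one direction, are needed. Even then Fisher's exact test on 4 v 0 gives p = 0.112.

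**Step 4. Pooled comparison.** Pooling the two sensing groups against the two control groups, 60 v 60, is an assumption; the protocol does not state it. Expected events become 60 x 0.05 = 3 to 60 x 0.10 = 6 per side. A true 6 v 6 (p = 1.00) read as 8 v 2 gives chi-squared p = 0.048 (Fisher 0.095). That takes six calls: two controls added and four sensing patients removed.

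**Step 5. Systematic tilt, for illustration only.** Take equal true recurrence in the pooled 60 v 60 comparison. Assume that 25-50% of recurrences in the sensing groups are not called AFL and that 2-5% of recurrence-free controls are wrongly called AFL. The exact chance of chi-squared p < 0.05 is:

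| True recurrence | No tilt | 25% missed, 2% over-called | 50% missed, 5% over-called |
|---|---|---|---|
| 5% | 4.6% | 10.8% | 37.7% |
| 10% | 5.0% | 12.4% | 42.9% |

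The spurious difference runs from 3.2 to 9.5 percentage points. The misreading rates are assumed; nothing in the protocol supports a particular value.

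**The case against.** **Silence is not a statement.** The protocol does not say that the reading is unmasked, and a site may in practice read recordings without the arm. This stands: the point is that no masking is specified. But silence permits unmasked reading.

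**The outcome is minor here.** It is one of a long list of secondary outcomes in a study that calls itself a feasibility study. The primary outcomes are procedural times and energy, which ECG reading does not touch. With 1.5-3 events per arm, the comparison will be weak even if masked. The 5-10% was seen over about eight months rather than six, and Potential Risks puts recurrent sustained arrhythmia after a failed procedure below 5%, so events may be fewer still. All of this stands and limits the weight of the point.

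**The reading is fairly objective.** Rhythm and a 30-second limit can be checked on the recording, and concomitant atrial fibrillation is excluded at entry. This reduces the room for judgement. It does not remove it, since atrial fibrillation can appear during follow-up.

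**Stronger readings that do not hold.** A reader might infer that one or two calls would decide the comparison; Step 3 shows that from equal counts they would not. A reader might also infer that the decision on repeat study biases the success rate. The protocol says "All patients who experience a recurrence will be offered a repeat electrophysiological study if clinically indicated", so that decision follows a recurrence and cannot change whether the patient counts as a success. It affects only which patients contribute to the separate outcome of isthmus re-conduction at repeat procedure.

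**Conclusion.** The point holds as a low-cost improvement. The protocol specifies no masking of the ambulatory ECG reading that determines freedom from AFL, while it states a directional expectation in favour of sensing.

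One reclassified patient is worth 3.3 percentage points of an arm's success rate, or 33-67% of its expected recurrences. This assumes that the quoted 5-10% applies to this six-month follow-up and that the patient's status rests on one episode. A significant result from equal counts would need at least four calls in one direction at 30 v 30. The size and direction of any actual bias cannot be derived from the protocol.

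A reader might infer that the follow-up assessments are known to be unmasked, or that the primary outcomes are affected. The protocol supports neither. Nor does it support asking, at no cost, that patients be kept unaware of their arm or that complications be judged from arm-free summaries: it does not describe who would do this or what it would take.

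**What to change.** Add to Protocol, Follow up, wording such as: *Ambulatory recordings will be labelled by study number only, without arm, catheter or mapping system. A member of the existing site staff who was not present at the procedure will record the rhythm and duration of each episode, against the definition of AFL lasting more than 30 seconds, before the arm is known.*

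The cost is minor coding work and keeping the procedure report apart from the recording. No patient, visit or test is added, and the sample size does not change. The protocol does not say who reads the recordings at present, so each site should confirm that a suitable member of staff is available. The benefit is confined to this secondary outcome: any remaining misreading should no longer depend on the arm.
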